### Intervention

All participants will receive their usual medical care, which may include adjuvant, neoadjuvant, or palliative treatment, specialist, nursing and other health outpatient appointments (eg, to see a physiotherapist) and visits to their general practitioner.

As part of the trial, all participants will be provided with written educational materials relating to different aspects of cancer recovery (eg, exercise, nutrition, and fatigue) via standardized print or digital material readily available from the hospital.

Usual care in the community involves very little exercise support in relation to exercise. As part of the trial, usual care also includes standardized verbal and written advice to complete physical activity in line with current recommendations (aim for 3 times weekly exercise for 30 minutes, including twice weekly strength training) [4]. All participants will also have the opportunity to discuss their ongoing rehabilitation needs at the end of the 8-week intervention period. They will be provided written information for referral to appropriate local services for ongoing support if required in line with usual practice at the health service.

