### Experimental Group: Exercise-Based Cancer Telerehabilitation

In addition to usual care, participants randomized to the experimental group (telerehabilitation) will receive a 60-minute group exercise delivered by a physiotherapist via videoconferencing (Zoom) twice-weekly for 8 weeks. Exercise will comprise cardiovascular and resistance training guided by published recommendations [4]. Exercise sessions will be individually tailored and include the use of free weights, resistance bands, body weight, and functional activities. Supervised aerobics (eg, marching in place and side-stepping) will comprise the cardiovascular component. Participants will be provided with an exercise band, and the exercise program will be supplemented by participants’ own exercise equipment or household items. The therapist will choose an exercise variation (eg, bicep curl using weights or with exercise band) based on the equipment available to the participant. Various upper- and lower-body stretches and balance exercises will be incorporated as required. Exercise intensity will be monitored during the exercise class using a Fitbit device (Fitbit Inspire) and modified Borg scale. The Fitbit will also be used for participants to self-monitor their physical activity levels throughout the 8-week intervention. A home exercise program will supplement exercise-based telerehabilitation sessions and be delivered via a web application (Physitrack). The home exercise program will encourage one additional 30-minute aerobic exercise session per week (eg, walking) during the intervention period and will be updated at the end of the rehabilitation program to encourage participants to conduct twice-weekly strength training and 3 times weekly aerobic training after the 8-week intervention period. Participants will also be provided education materials relating to different aspects of cancer recovery (eg, nutrition, emotions, and fatigue) via a web-based information portal (iLearn, Totara Learning Solutions, Wellington, New Zealand) (Table 1).

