**When and how much**					
	Intensity	Cardiovascular: moderate (BORG 3-5, maximum heart rate=60%-85%) Resistance: 2-3 sets with 10-12 repetitions Participants progressed when completing 3 sets with 10-12 repetitions until fatigue		Advised to undertake physical activity in accordance with current physical activity recommendations: advised to undertake physical activity in accordance with current physical activity recommendations Moderate activity (cardiovascular: maximum heart rate=60%-85%, resistance=2-3 sets, 10-12 repetitions)	
	Frequency	2× weekly supervised 1× weekly unsupervised		Advised to participate in 3x weekly unsupervised physical activity	
	Session time	60-minute web-based exercise group 30-minute unsupervised exercise session		Advised to complete 30-minute unsupervised physical activity	
	Overall duration	8 weeks		8 weeks	
	Tailoring	Individualized exercise program based on initial consultation and goals		None	
	Trial fidelity	Physiotherapists who are employed by the health service to provide the intervention will receive training and mentoring by a senior research physiotherapist with oncology experience Electronic exercise log via the Physitrack app and Fitbit Inspire Records of the content, number, and duration of completed web-based group sessions Clinical supervision of therapists in accordance with standard health service policy Exercise interventions that patients have participated in outside of the trial will be recorded		Physiotherapists who are employed by the health service to provide assessment and advice will receive training and mentoring by a senior research physiotherapist with oncology experience Clinical supervision of therapists in accordance with standard health service policy Exercise interventions that patients have participated in outside of the trial will be recorded	

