### Study Outcomes

Participants will complete an assessment of health-related quality of life at weeks 0, 9, and 26. Immediately post intervention (week 9) is the primary end point. Walking capacity and self-efficacy will also be assessed at weeks 0 and 9. Physical activity and health service usage utilization will be assessed at weeks 0 and 26. A clinician blind to group allocation will complete the assessments. Primary and secondary outcomes are outlined in Table 2.

**Table 2 table2:** Primary and secondary outcomes.

Outcomes		Measures or sources	Definitions	Time points

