**Secondary outcomes**				
	Physical activity	activPAL accelerometer	Time spent in moderate to vigorous activity, walking, sitting, and step count before and after the intervention. Participants will wear the activity monitor continuously for 8 consecutive days. Only complete 24-hour recording days will be included for analysis. However, as monitors may need to be removed for the purpose of swimming or bathing, evidence of nonwear matching with an activity logbook will still be included.	Week 0 Week 26
	Physical capacity	6-Minute walk test	Walk distance (in meters) before and after the intervention.	Week 0 Week 9
	Self-efficacy for physical activity	Questionnaire developed using the Health Action Process Approach [34] (Multimedia Appendix 2)	Score on the self-efficacy questionnaire for physical activity before and after the intervention.	Baseline Week 9
	Emergency department presentations	Hospital database and electronic medical record	Number of emergency department presentations during the trial period.	Week 26
	Hospital readmissions	Hospital database and electronic medical record	Number of hospital readmissions during the trial period, associated inpatient days, and duration between with each admission.	Week 26
	Health service utilization	Questionnaire (Multimedia Appendix 3)	Frequency of allied health and medical services, pharmaceutical use, and hospital admissions (external to the health network).	Week 0 Week 26
	Audit of exercise interventions	Questionnaire	Frequency, type, and duration of any exercise interventions completed outside the trial.	Week 9 Week 26

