### Statistical Analysis

#### Analysis of Quantitative Data

The primary outcome (postintervention global health–related quality of life) will be analyzed using linear mixed effects models. Modeling will account for variation in baseline values. This method accounts for within-participant dependence of observations over time, and for missing data, allowing some participants to have missing observations at certain time points. If more than 5% of data are missing, a multiple imputation process will be used, providing the assumption that data are missing at random is met. A similar approach will be used for analysis of secondary continuous outcomes collected longitudinally. The time spent in moderate to vigorous physical activity will be estimated using a cut-off of 100 steps per minute for moderate-intensity physical activity [40]. The proportion of participants meeting physical activity guidelines will be described and compared using risk ratios. The number of emergency department and hospital admissions will be reported as an incidence rate ratio using a negative binomial regression model. To avoid bias and to maximize the randomization process, all available data will be analyzed in accordance with allocation (intention-to-treat analysis) regardless of adherence.

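### The guideline behind the physical activity proportion is not named, and the listed measures can support only its aerobic (stepping) part, not the strength training that the trial recommends

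*Protocol article*

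**What the plan says.** Under Analysis of Quantitative Data, moderate-to-vigorous time is to be derived "using a cut-off of 100 steps per minute for moderate-intensity physical activity". The next sentence sets up a binary comparison: "The proportion of participants meeting physical activity guidelines will be described and compared using risk ratios". It gives no guideline, threshold, time point or data source.

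The trial's own recommendation appears in two places:

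- The Intervention section describes the advice that forms part of usual care in the trial: "aim for 3 times weekly exercise for 30 minutes, including twice weekly strength training".
- The section on the experimental group says that the home programme is updated at the end of the rehabilitation programme to "encourage participants to conduct twice-weekly strength training and 3 times weekly aerobic training after the 8-week intervention period".

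Table 1 also lists resistance sets and repetitions in the activity advice to the comparison group.

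On measurement, Table 2 gives the activPAL as the physical activity instrument, with these variables: "Time spent in moderate to vigorous activity, walking, sitting, and step count before and after the intervention". On timing, Study Outcomes says: "Physical activity and health service usage utilization will be assessed at weeks 0 and 26". Two other sources touch on exercise. One is a questionnaire at weeks 9 and 26 on "Frequency, type, and duration of any exercise interventions completed outside the trial". The other is an "Electronic exercise log via the Physitrack app and Fitbit Inspire", which Table 1 lists in the experimental column only.

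**The concern.** Each version of the recommendation has a strength element. The activity outcome consists of stepping, sitting and cadence, and bands, free weights and body-weight work need not produce steps at 100 per minute. A participant who walks briskly and does no strength work could be counted as meeting the guideline. One who does the strength work could be missed. On a literal reading of the Intervention wording, strength work may fill two of the three weekly sessions, so a full complier might show qualifying cadence in only one.

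The risk is a published statement about meeting guidelines that the data cannot support. Strength uptake may also differ by arm: the experimental group has supervised resistance training and a home programme, while the comparison group has advice.

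**Working it through.** **Step 1. Figures in the plan.** The article gives no figure for this endpoint. Its sample size reproduces. A two-sided t-test at 0.05 with 80% power, difference 10 and SD 18 needs 51.84, so 52 per arm and 104 in total, taking 1:1 allocation as an assumption. Then 104 / 0.90 = 115.6, so 116. Nothing below changes this.

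**Step 2. Can any listed source classify the strength element in both arms?**

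| Source | Arms | Time | Records strength training? |
|---|---|---|---|
| activPAL | both | weeks 0, 26 | no such variable listed |
| Exercise questionnaire | both | weeks 9, 26 | only as part of an exercise intervention outside the trial |
| Physitrack and Fitbit log | experimental | not stated for the log | not available for usual care |

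As worded, the questionnaire would leave out the trial's own home programme and may leave out self-directed strength work. No source covers strength training equally in both arms.

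**Step 3. Effect on the risk ratio.** Take the full recommendation as the aerobic part plus the strength part. Let *a* be the proportion meeting the aerobic part and *s* the proportion of those who also do the strength work, in experimental (E) and control (C).

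RR(full) = (a_E × s_E) / (a_C × s_C) = RR(aerobic) × (s_E / s_C)

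All inputs below are assumptions; the documents give none.

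| a_C, a_E | s_C, s_E | RR aerobic | RR full | Factor |
|---|---|---|---|---|
| 0.40, 0.50 | 0.50, 0.50 | 1.25 | 0.25/0.20 = 1.25 | 1.0 |
| 0.30, 0.30 | 0.50, 0.70 | 1.00 | 0.21/0.15 = 1.40 | 1.4 |
| 0.30, 0.40 | 0.30, 0.60 | 1.33 | 0.24/0.09 = 2.67 | 2.0 |

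In the first row the ratio is unaffected, but the proportions reported (40% and 50%) are twice those for the full recommendation (20% and 25%).

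**Step 4. Baseline activity.** The simulation used 52 per arm, 2,000 replicates, true proportions of 30% and 50% (log risk ratio ln(0.50/0.30) = 0.511), and a baseline score correlated with the continuous score underlying the outcome. The adjusted estimate came from a logistic model standardised to a risk ratio.

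| Baseline correlation | Mean log RR, unadjusted | Mean log RR, adjusted | Variance ratio, adjusted/unadjusted |
|---|---|---|---|
| 0.3 | 0.524 | 0.524 | 0.96 |
| 0.5 | 0.527 | 0.525 | 0.87 |
| 0.7 | 0.533 | 0.528 | 0.70 |

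Both estimates sit close to 0.511, so leaving baseline out adds no material bias. Adjustment lowers the variance by about 4% to 30%. A modified Poisson model fitted to the same simulated data gave variance ratios of 0.97, 0.90 and 0.80, a somewhat smaller gain of about 3% to 20%.

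**The case against.** The best reply is that the article simply leaves a derived variable undefined, and that a guideline, threshold and time point belong in the full protocol or analysis plan. An aerobic-only threshold may be what is meant. That is fair as far as the definition goes. It does not cover the measurement gap, because an analysis plan can choose a threshold but cannot recover data that no listed source collects. If an aerobic threshold is meant, the label still claims more than is measured, given what participants are told to do.

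The questionnaire could show a structured strength programme at week 26, and its items are not shown in the article. The article does not link it to this endpoint, however, and its stated scope is narrower than strength training in general.

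Both arms receive the same strength advice, and week 26 falls 18 weeks after the 8-week programme ends. Uptake may then be similar, in which case the risk ratio stands. This is why the size can only be conditional.

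Three stronger readings are tempting, and the article supports none of them:

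- **That guideline status will be judged from cadence.** This is an inference from two adjacent sentences and the only listed activity instrument. The text does not say so.
- **That the risk ratio ignores baseline activity.** The article states baseline adjustment for the primary outcome and a similar approach for continuous secondary outcomes. For the risk ratio it neither states nor excludes it. An unadjusted risk ratio is valid under randomisation.
- **That the endpoint misses half of the intervention, or that the risk ratio is wrong by a particular large factor such as 3.** The article gives no split between cardiovascular and resistance work, and no uptake figures.

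**Conclusion.** The point holds in a limited form. The guideline is unnamed, the recommendation given to participants includes strength training, and the listed measures cannot establish in both arms whether it was done. The data support a claim about the aerobic component and no more.

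The consequence for the risk ratio depends on the ratio of strength uptake between arms: none if uptake is equal, a factor of 1.4 at an assumed 70% against 50%, and 2 at an assumed 60% against 30%. A ratio below 1 would move it the other way. With equal uptake only the proportions are overstated, twofold if half of those meeting the aerobic part do the strength work. These factors also assume that the full recommendation is the aerobic part plus the strength part. If strength sessions may count among the three weekly sessions, misclassification runs in both directions and this simple factor does not apply.

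The baseline question concerns precision only. The proportion is a secondary analysis without its own row in Table 2, so the importance is low.

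**What to change.** Name the guideline, the threshold and the time point, and state which of the trial's two descriptions of the recommendation, if either, the endpoint refers to. Then choose one of two routes:

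1. **Relabel.** Define the endpoint as meeting the aerobic component at week 26, from activPAL minutes at or above 100 steps per minute against a stated threshold, and report it under that name. This costs only wording, and the price is a narrower endpoint name.
2. **Add an item.** If the full recommendation is meant, add one question on weekly strength sessions, asked of both arms, to the existing week-26 exercise questionnaire. The item would have no baseline value and would rest on self-report. Recruitment began in April 2022, so no week-26 assessment was due by the June 2022 report of 14 enrolled. Anyone assessed at week 26 before the item is added would lack it.

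As an option, estimate the risk ratio with adjustment for baseline moderate-to-vigorous minutes, which are already collected. Either a modified Poisson model or a standardised logistic model serves. In the simulation above the latter gained more precision. Fix the choice before group data are seen. It costs a sentence in the analysis plan.

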**What procedures**					
	Provider	One physiotherapist with oncology experience provided by the hospital will provide exercise guidelines in verbal and written format and the web-based group intervention One allied health assistant will support the web-based group intervention		Usual care team (eg, specialist, general practitioner, and allied health professional) One physiotherapist with oncology experience provided by the hospital will provide exercise guidelines in verbal and written format	
	How	Supervised sessions via videoconference supplemented by web-based information above Physical activity device for remote exercise and physical activity monitoring		In person or via telehealth as available	
	Where	Intervention clinicians are clinic-based Participants receive an exercise program at home Participants continue to receive usual cancer care in hospital or at home as indicated		Participants receive usual care in hospital or at home as indicated	

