Total direct costs to the health service for each participant will be determined from the intervention costs and cost of health services utilized over 6 months as recorded from hospital administrative data and health service utilization questionnaire. Costs associated with delivering telerehabilitation will be attributed to the experimental group and cost associated with usual care will be attributed to the comparison group. These will be determined from a register of staff and the time engaged in telerehabilitation or usual care for each participant. Labor costs will be attributed to the staff member and the cost of the telerehabilitation intervention and usual care (based on time and location) to determine a total intervention cost for each participant as well as infrastructure costs. Total costs for each participant will be determined from the intervention costs, the cost of health services utilized over 6 months for experimental group participants, and the cost of health services utilized over 6 months for comparison group participants. The incremental cost-effectiveness ratio will be calculated as the difference in total program and health service costs per mean difference in the global quality-of-life score between the comparison and experimental groups over 6 months. A cost utility ratio will be calculated on the basis of the EORTC-QLQ C30 global quality-of-life score [41] as the change in total program and health service cost per change in quality-adjusted life years saved in the experimental and comparison groups over 6 months.

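### The costing rule treats telerehabilitation and usual care as alternatives although the trial adds one to the other; read as written, it lowers the incremental cost by the trial-delivered usual care

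*Protocol article*

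**What the plan says.** The attribution rule is in the economic paragraph of Analysis of Quantitative Data: the cost of delivering telerehabilitation goes to the experimental group, and "cost associated with usual care will be attributed to the comparison group". On the data source, the next sentence says: "These will be determined from a register of staff and the time engaged in telerehabilitation or usual care for each participant". The paragraph then adds the cost of six months of health service use in each arm. It uses the between-group difference in programme plus health service cost as the numerator of both the cost-effectiveness and the cost-utility ratio.

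The description of the arms is different in kind:

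- The Experimental Group section states: "In addition to usual care, participants randomized to the experimental group (telerehabilitation) will receive a 60-minute group exercise".
- The Intervention section opens with "All participants will receive their usual medical care" and says that, within the trial, "usual care also includes standardized verbal and written advice to complete physical activity in line with current recommendations". It also gives written educational material to everyone, and offers everyone a discussion of further rehabilitation needs when the eight weeks end.
- Table 1, Provider row, says of the physiotherapist in the experimental column: "One physiotherapist with oncology experience provided by the hospital will provide exercise guidelines in verbal and written format and the web-based group intervention". The comparison column lists the same guideline provision, without the group. Written information on local exercise services appears in both columns.

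**The concern.** The attribution sentence gives each arm one cost, as if telerehabilitation replaced usual care. The arms as described differ by telerehabilitation alone, and the trial-delivered usual care is common to both. A cost that is common to both arms should cancel in the increment. If it is charged to the comparison arm and not to the experimental arm, it is instead subtracted from the cost of telerehabilitation.

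The error has a fixed direction and enters the numerator of both economic ratios. The Discussion states cost-effectiveness as a hypothesis and describes cost as a main driver of health care decisions. The rule may also shape data capture: usual-care minutes that are never logged for experimental participants are hard to recover later. The primary quality-of-life analysis is not touched.

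**Working it through.** The article reports no cost or ratio, so there is no figure of its own to reproduce. The check is algebra on the stated rule, followed by an illustration of size.

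**Notation, per participant**

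- T: cost of delivering telerehabilitation.
- U: cost of trial-delivered usual care (exercise advice, written materials, referral discussion), taken as equal in the two arms because the article describes it in the same terms for both.
- H_E, H_C: six-month health service cost in the experimental and comparison arms.

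**Increment under each rule**

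1. As written: (T + H_E) − (U + H_C) = T − U + (H_E − H_C).
2. Add-on design, U charged in both arms: (T + U + H_E) − (U + H_C) = T + (H_E − H_C).
3. Difference, rule 1 minus rule 2: −U.

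Charging U to neither arm gives the same increment as rule 2. Usual medical care sits in H_E and H_C, which appear in both rules, so it contributes nothing to the difference. Both ratios share this numerator, so each is lowered by U divided by its own denominator.

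**Illustration in staff time**

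Inputs from the article: twice-weekly sessions for 8 weeks, which is 2 × 8 = 16 sessions; 60 minutes each; one physiotherapist and one allied health assistant; about 6 participants per group. Assumptions: both staff attend throughout, groups are full, and usual-care contact takes 0.5 to 1.0 staff-hour. The article gives no figure for that contact time.

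- Group-session labour per participant: 16 × 1 × 2 / 6 = 5.33 staff-hours.
- Increment under the rule as written: 5.33 − 0.5 = 4.83 hours, or 5.33 − 1.0 = 4.33 hours.
- Shortfall: 0.5 / 5.33 = 9.4%, or 1.0 / 5.33 = 18.8%.

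These percentages apply to group-session labour only. T also includes programme set-up, the activity tracker, the exercise band, platforms and infrastructure. All of these enlarge T and reduce the percentage.

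**Illustration in money**

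With wholly assumed values of T from 500 to 2000 and U from 25 to 200 currency units, and H_E = H_C, U / T runs from 25 / 2000 = 1.25% to 200 / 500 = 40%. The upper end pairs the cheapest programme with the dearest advice. At T = 1000, U = 50 and a 10-point quality-of-life difference (the sample-size target), the ratio is 950 / 10 = 95 per point as written, against 1000 / 10 = 100.

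**The case against.** The best defence is that the sentence merely names the programme that defines each arm. It does not contain the word only, and it does not say that usual-care time in the experimental arm is excluded. The register works participant by participant and could hold usual-care time for either arm. Table 1 lists the exercise guidelines together with the group sessions as the experimental provider's task, so their cost might be booked under telerehabilitation, and then nothing would be lost. A journal article also condenses, and detailed costing rules may stand elsewhere.

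Part of this stands. The understatement is conditional on following the sentence as written, and a careful costing team could avoid it. But no sentence says that usual-care time is charged to the experimental arm, and the register sentence keeps the either-or form. Nor is this a detail left to another document: the article states a rule, and that rule does not fit its own design.

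A reader might go further and infer that all usual-care cost is missing from the experimental arm. The article does not support that. Appointments, allied health contacts, medicines and admissions are collected with no restriction by arm (Table 2), and six-month use is costed for both groups. Only the trial-delivered package is exposed.

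There is a smaller related risk. Table 1 names the usual care team as provider in the comparison column only. If its contacts were booked as programme cost as well as health service use, the comparison arm would be charged twice. The article does not say that this will happen, but it does not exclude it.

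**Conclusion.** The point holds in this limited form. The attribution sentence conflicts with the add-on design. Applied as written, it lowers the incremental cost by U per participant, in favour of telerehabilitation, in both economic ratios. This assumes that U is the same in the two arms and that U is not booked in the experimental arm under another label.

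The size cannot be derived from the article. It is probably small, since advice, booklets and one discussion are set against sixteen supervised hours with two staff. The 9% to 19% must not be read as the bias in either ratio: it rests on an assumed contact time, covers group-session labour alone, and leaves out the difference in health service cost, which is also part of the numerator. The sentence should be corrected because the direction is fixed and the correction is cheap.

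**What to change.** Replace the attribution sentence with a rule to this effect: *Trial-delivered usual care (exercise advice, written materials, referral discussion) is recorded in the staff register and charged for every participant in both arms. The cost of telerehabilitation (staff, devices, exercise band, platforms, infrastructure) is added in the experimental arm only. Six-month health service use is added in both arms, and contacts already in the register are not counted again there.*

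The register must then explicitly log usual-care time for experimental participants too; the article does not show that it already does. Where that time was not logged for participants already enrolled, a standard time per contact could be used and declared as an assumption, since the advice is standardized. The cost is a few lines of text, a little more logging, and a slightly less favourable incremental cost for telerehabilitation.
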